## Abstract

**Background:**

Loss of dignity for people with advanced cancer is associated with high levels of psychological and spiritual distress and the loss of the will to live. Dignity Therapy is a brief psychotherapy, which has been developed to help promote dignity and reduce distress. It comprises a recorded interview, which is transcribed, edited then returned to the patient, who can bequeath it to people of their choosing. Piloting in Canada, Australia and the USA, has suggested that Dignity Therapy is beneficial to people with advanced cancer and their families. The aims of this study are to assess the feasibility, acceptability and potential effectiveness of Dignity Therapy to reduce psychological and spiritual distress in people with advanced cancer who have been referred to hospital-based palliative care teams in the UK, and to pilot the methods for a Phase III RCT.

**Design:**

A randomised controlled open-label trial. Forty patients with advanced cancer are randomly allocated to one of two groups: (i) Intervention (Dignity Therapy offered in addition to any standard care), and (ii) Control group (standard care). Recipients of the 'generativity' documents are asked their views on taking part in the study and the therapy. Both quantitative and qualitative outcomes are assessed in face-to-face interviews at baseline and at approximately one and four weeks after the intervention (equivalent in the control group). The primary outcome is patients' sense of dignity (potential effectiveness) assessed by the Patient Dignity Inventory. Secondary outcomes for patients include distress, hopefulness and quality of life. In view of the relatively small sample size, quantitative analyses are mainly descriptive. The qualitative analysis uses the Framework method.

**Discussion:**

Dignity Therapy is brief, can be delivered at the bedside and may help both patients and their families. This detailed exploratory research shows if it is feasible to offer Dignity Therapy to patients with advanced cancer, many of whom are likely to be in the terminal stage of their illness, whether it is acceptable to them and their families, if it is likely to be effective, and determine whether a Phase III RCT is desirable.

**Trial registration:**

Current Controlled Clinical Trials: ISRCTN29868352

## Background

There has been much progress in the assessment and treatment of the somatic symptoms of people with advanced cancer, however less is known about assessing and treating psychosocial, existential and spiritual issues. Loss of dignity for people with advanced cancer is associated with high levels of psychological and spiritual distress and the loss of the will to live[1]. For some people, a sense that nothing of one's life will be transcendent of death was associated with loss of dignity, and many felt that maintaining dignity was highly dependent on how they perceived themselves to be seen by others. It is therefore crucial to develop and evaluate interventions to address these needs. An empirically based model of dignity in the terminally ill has been developed in Canada from interviews with 50 people with advanced cancer focussing on what supports and what undermines their dignity [2,3]. The model comprises three major categories (illness-related concerns, dignity conserving repertoire, social aspects of the illness experience), which refer to broad issues that determine how individuals experience a sense of dignity as death approaches. Each of the three categories has several themes and sub-themes. The model provides a theoretical framework, which helps understanding of how people with advanced cancer may experience a loss of dignity and provides the theoretical base for a therapeutic intervention: dignity therapy[4].

Dignity Therapy is a brief, individualized intervention to increase the sense of purpose, meaning and worth and reduce spiritual and psychological suffering for people with advanced cancer. The therapy can be delivered at the bedside by health care professionals (after brief training). The therapist conducts an interview, which is based on the dignity model[2]. Individuals are offered the opportunity to address aspects of life they feel most important, such as recounting parts of their life they feel proudest of, things they feel are or were most meaningful, the personal history they would most want remembered, or advice to their family and friends. Interviews last between 30 and 60 minutes. They are tape recorded, transcribed, edited, (see methods for details of editing procedure) and quickly returned to the patient to share with people of their choosing. These 'generativity' documents allow people to leave behind something lasting. An important feature of the therapy is that it also has the potential to help friends and relatives in their bereavement[5].

A preliminary evaluation of Dignity Therapy conducted with patients with advanced cancer in Canada and Australia have produced positive findings for patients[4] and their families[5]. Ninety-one percent of participants reported being satisfied with dignity therapy; 76% reported a heightened sense of dignity; 68% reported an increased sense of purpose; 67% reported a heightened sense of meaning; 47% reported an increased will to live; and 81% reported that it had been, or would be of help to their family. Randomised controlled trials (RCTs) of Dignity Therapy for hospice patients are underway in Canada, Australia and the USA, assessing outcomes immediately after the intervention. However, the longer term impact of the intervention on patients is not being assessed. Furthermore, since responses to Dignity Therapy may be influenced by a range of important social and cultural factors, the results of these trials may not be generalisable to the UK. There are a number of potential moderators of the impact of intervention (e.g. ethnicity, age, cognitive acuity, stage of illness, baseline levels of distress). Answering these questions would require a randomised controlled trial in the UK. There are a number of methodological and ethical issues concerning conducting RCTs of patients with advanced cancer[6], including concerns about randomisation, loss to follow-up and appropriate user involvement in the research.

In-depth piloting, which includes an exploration of the feasibility of delivering an intervention and attention to the context in which interventions take place, as planned here, is recommended in the new Medical Research guidance for developing and evaluating complex interventions[7]. As recommended in the MRC framework, we are also testing our proposed outcome measures. The results will inform the design of a Phase III RCT.

## Aims and objectives

The aims of the study are to assess the feasibility, acceptability and potential effectiveness of Dignity Therapy to reduce psychological and spiritual distress in people with advanced cancer who have been referred to hospital-based palliative care teams. The specific objectives are to:

a) Determine whether Dignity Therapy is likely to increase peoples' sense of dignity or reduce psychological or spiritual distress.

b) Determine whether it is feasible to provide Dignity Therapy in this setting.

c) Determine whether Dignity Therapy is acceptable to patients and their families.

d) Pilot methods for a larger (Phase III) RCT (e.g. recruitment, randomization, follow-up, suitability of measures, effect size).

## Methods

### Study design

A Phase II open-label RCT comprising two groups: (i) Intervention (Dignity Therapy offered in addition to standard care), and (ii) Control group (standard care). Standard care comprises assessment by a multi-professional palliative care team, including nurses, a psychosocial worker and doctors trained in providing psychosocial support. Consenting participants have been randomly allocated to one of these two groups after baseline (T1) measures have been collected.

### Randomization

Randomization was conducted by an independent statistician. Treatment allocation (Dignity Therapy or control) was performed by block randomization with a fixed block size of two. Allocation concealment is facilitated by using sequentially numbered opaque sealed envelopes for consecutive and eligible participants. To reduce the risk of bias, the research assistant opens the next envelope in the presence of the patient to ascertain which group the patient has been allocated to after baseline measures have been collected from participants.

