### Participants

The sample will comprise 40 adults with advanced cancer who have been referred to hospital-based palliative care teams working in two NHS Trusts, and who are well enough to participate in a protocol lasting two weeks. For this pilot study, we are obtaining in-depth information on taking part in the study and receiving the therapy from a relatively small sample rather than planning to detect significant group differences. One of the aims of the study is to estimate the effect size for an RCT.

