### Recruitment procedure

The recruitment and follow-up procedure is shown in Figure 1. Potential participants are identified by palliative care teams from their lists. For patients recruited from one NHS Trust, these are in-patients or those visiting out-patient clinics. The research assistant gives potential participants an invitation letter and patient information sheet after being introduced by the palliative care team. The research assistant visits patients at least 24 hours later to find out if they are interested in taking part. From the other Trust we are recruiting patients cared for in the community. The clinical nurse specialist visiting the patient will give them the invitation letter and patient information sheet. They will be asked to send a reply slip to the research team or to notify the Clinical Nurse Specialist of their decision to take part or not. Patients are encouraged to discuss involvement in the study with family or friends before deciding whether or not to take part.

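### A fixed block size of two in an open-label trial lets every second allocation be deduced before that patient is randomised, so sealed envelopes do not secure concealment

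*Protocol article*

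**What the plan says.** The Randomization section of the protocol article gives the scheme: "Treatment allocation (Dignity Therapy or control) was performed by block randomization with a fixed block size of two". An independent statistician conducted the randomisation. Concealment is said to rest on "sequentially numbered opaque sealed envelopes for consecutive and eligible participants". After baseline measures have been collected, "the research assistant opens the next envelope in the presence of the patient to ascertain which group the patient has been allocated to", a step the section presents as reducing the risk of bias.

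The Study design section describes "A Phase II open-label RCT comprising two groups". The Participants section sets the size: "The sample will comprise 40 adults with advanced cancer".

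The Recruitment procedure section gives the research assistant further tasks. At the hospital Trust this role hands over the invitation after an introduction by the palliative care team, and returns at least 24 hours later. It then obtains written consent. The second Trust works differently: "From the other Trust we are recruiting patients cared for in the community", and there a clinical nurse specialist gives out the invitation.

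The article mentions neither varying block sizes nor withholding the block size from recruiting staff. It prints the size while parts of the text describe recruitment as still in progress.

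**The concern.** Concealment means that nobody who influences entry can foresee the next allocation. An opaque envelope prevents someone from reading the assignment. It cannot prevent someone from working it out. With two arms and blocks of two, the second patient of each pair must receive whatever the first did not. In an open-label trial the first assignment is common knowledge to the research assistant, who opened that envelope. Even someone not told the block size could infer it from a short run of opposite pairs.

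The role with this knowledge is well placed to act on it, perhaps without intending to. It takes consent, approaches hospital patients, and is present when the baseline Patient Dignity Inventory is completed. Entry also involves judgement, since the palliative care team decides whether a patient can manage a two-week protocol, and contacts can be rescheduled. Opening the envelope after baseline therefore protects the baseline data only in the first slot of each pair.

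The outputs at stake are those the pilot exists to produce. The Aims and objectives section lists randomisation, recruitment and effect size among the methods being piloted, and the Participants section says an effect size is to be estimated for a later RCT.

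**Working it through.** The plan gives no predictability figure and no power calculation, so there is no stated result to reproduce. The check needs only three inputs from the protocol article:

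- block size 2, fixed (Randomization)
- two arms (Design, in the Abstract: "Forty patients with advanced cancer are randomly allocated to one of two groups")
- N = 40 (Participants)

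**Certain allocations under the current scheme.** There are 40 / 2 = 20 blocks. In each, the second allocation is the opposite of the first with probability 1. That gives 20 certain allocations, or 20 / 40 = 50%. If each Trust had its own list, which the article does not say, the count would hardly change: 10 + 10 = 20 for a 20/20 split, and 12 + 7 = 19 for 25/15.

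**Correct-guess rate.** First slots are guessed right half the time and second slots always: 0.5 × 0.5 + 0.5 × 1 = 0.75, or 30 of 40. Simple randomisation would give 50%.

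**Other fixed block sizes.** For a known block of size 2b, the certain share is 1/(b + 1). The expected number of correct guesses per block is b + (4^b / C(2b, b) − 1)/2.

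| Block size | Certain share | Certain of 40 | Correct guesses per block | Guess rate |
|---|---|---|---|---|
| 2 | 1/2 = 50% | 20 | 1 + (4/2 − 1)/2 = 1.5 | 75.0% |
| 4 | 1/3 = 33% | 13.3 | 2 + (16/6 − 1)/2 = 2.83 | 70.8% |
| 6 | 1/4 = 25% | 10 | 3 + (64/20 − 1)/2 = 4.1 | 68.3% |

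**Randomly mixed blocks of 4 and 6.** I simulated lists of 40 against a guesser who knows that the sizes are 4 and 6 and sees every past allocation, but does not know the current block's size. On average 2.3 of 40 allocations are certain (about 6%), and 27.6 of 40 guesses are right (about 69%). The same method returns exactly 20 and 30 for the current scheme.

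**Possible size of bias (assumption, not a figure from the document).** On average half of each arm sits in second slots. Suppose that steering shifts expected outcome in those slots by g SD.

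- Steering in opposite directions for the two arms: 0.5g + 0.5g = g.
- Steering at one arm's slots only: 0.5g.

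For an assumed g of 0.1 to 0.3 SD, the bias is 0.1 to 0.3 SD in the first case and 0.05 to 0.15 SD in the second. For scale, the standard error of the group difference with 20 per arm and no attrition is √(1/20 + 1/20) = 0.32 SD.

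**The case against.** The best defence has several parts.

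*Timing.* A reader might infer that half of the allocations are known before the patient is approached. The text does not support that. The hospital visit to seek agreement comes at least 24 hours after the invitation, several patients may be in process at once, and in the community Trust a nurse makes the approach. The relevant slot may become deducible only by consent or baseline. This part stands, but consent and baseline still precede randomisation, so concealment is not restored.

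*No evidence of misuse.* A reader might also infer that concealment actually failed for half the sample. The article does not show that the recruiter knew the block size or acted on it, and nothing says the palliative care teams were told the running sequence. Assigning envelopes to consecutive eligible participants also narrows the room to choose. This stands as a limit on the claim. It does not make the allocations unpredictable.

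*Drop-out.* Patients leave after allocation, when the arm is open under any block scheme. Predictability could affect drop-out only indirectly, through who was enrolled.

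*Stratification.* The article does not describe stratification by Trust. In a pilot of 40 that is a design preference, a condensed article may omit it, and it is separate from concealment. It forms no part of this point.

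*Small descriptive pilot.* The Analyses section calls the analysis mainly descriptive, and the illustrative bias is no larger than one standard error. That lowers the severity. It does not remove the problem, because a biased effect size would feed into planning Phase III.

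**Conclusion.** The point holds in limited form. With a fixed block of two, 20 of 40 allocations (50%) follow with certainty from the previous one, and the best guess is right for 75%. This applies to anyone who knows or infers the block size and saw the previous allocation. The research assistant role saw every one, and the article describes no step that keeps the block size from it. The sealed envelopes therefore do not give the concealment the Randomization section relies on.

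The 50% and 75% are exact given the stated design. Any bias in SD units rests on an assumed degree and direction of steering, for which the document offers no evidence; the values above are illustrations only. The flaw should be fixed, but it does not by itself invalidate a small, mainly descriptive pilot.

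**What to change.** **Unopened envelopes.** The independent statistician generates a new list with randomly varying permuted blocks, for example of 4 and 6. The sizes are withheld from the research assistant, therapist and clinical teams, and are not published until recruitment ends. The patient's identifier is written on the envelope before it is opened, which ties each envelope to one patient. Over a full list of 40, certain allocations fall from 20 to about 2 and the guess rate from 75% to about 69%. The main gain is the loss of certainty; guessing remains better than chance. Parts of the article report randomisation in the past tense, so the number of envelopes left is unknown, and the benefit shrinks with it.

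**Patients already randomised.** Report the predictability as a limitation of the effect-size estimate. Comparing first-in-pair with second-in-pair patients is tempting but would settle little. With about 10 patients per cell, the standard error of the difference between the two effects is √(4/10) = 0.63 SD, a 95% half-width of 1.96 × 0.63 = 1.24 SD.

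**Phase III.** Do not carry the scheme forward.

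**Cost.** One new list, one set of envelopes and a short amendment. The arms may end slightly unequal. Even a pessimistic 23:17 split keeps 4 × 23 × 17 / 40² = 97.8% of the efficiency of 20:20.

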### Ethical Approval

This study has been approved by The King's College Hospital Research Ethics Committee (10/11/2008, ref: 08/H0808/155), and meets the requirements of the local Research Governance Framework.

### Participants

The sample will comprise 40 adults with advanced cancer who have been referred to hospital-based palliative care teams working in two NHS Trusts, and who are well enough to participate in a protocol lasting two weeks. For this pilot study, we are obtaining in-depth information on taking part in the study and receiving the therapy from a relatively small sample rather than planning to detect significant group differences. One of the aims of the study is to estimate the effect size for an RCT.

#### Inclusion criteria

Patients with a diagnosis of cancer aged 18 years or over are included. We are not selecting people on the basis of prognosis or stage of disease, however, since patients are receiving palliative care, most are expected to have advanced cancer. Participants are not screened for spiritual or psychological distress, or loss of dignity, however, these are assessed at baseline to explore the potential moderating effects of these variables on the impact of the intervention.

#### Exclusion criteria

Patients are excluded if the palliative care team feel they are unable to take part in a protocol lasting two weeks (the time taken to collect baseline measures and complete the intervention), or if they are unable to provide informed consent either due to cognitive problems or the severity of their illness, or because they are unable to understand English. Patients with moderate or severe cognitive impairment are excluded since their 'generativity' documents are likely to reflect a fractured sense of self, which could be distressing to them and recipients of these documents.

A close family member or friend (for participants in both groups) is invited into the study to obtain their views on taking part in the study and the therapy (intervention group only). These are usually the recipients of the 'generativity' documents, however, any additional recipients will also be invited to take part to obtain their views on the therapy.

### The intervention

The therapy is delivered by a palliative care nurse who has been trained in Dignity Therapy by [name] (who developed it). Training included the theoretical basis for the intervention, demonstrations of Dignity Therapy, a detailed overview of the therapy manual, editing the therapy documents and working with patients to produce a document that will be helpful for them and its recipients.

A standard framework of questions used in the therapy (Appendix 1) is given to patients in the intervention group (after randomization) to give them the opportunity to think about their responses before the session. The question framework provides a flexible guide for the therapist to shape the interview, based on patients' level of interest and responses. The therapist follows the patients' cues, helping them to structure and organise their thoughts, for example, by asking questions about time sequences, how events are causally related to each other and facilitating the disclosure of thoughts, feelings and memories. If a patient prefers a friend or relative to be present during the dignity therapy session, they can either listen or join in. Patients sometimes find they need help to recall details. This strategy has proved to be very helpful for some patients in the piloting of Dignity Therapy in Canada, Australia & USA. The role of the person sitting in will be agreed with the patient beforehand, and the therapist will ensure that the discussion is led by the patients rather than their friends or relatives.

These interviews are tape-recorded, quickly transcribed verbatim then shaped into a narrative using a formatted editing process. This includes clarifications to eliminate colloquialisms, non-starters and irrelevant sections (such as interruptions), chronological corrections, tagging and editing any content that might inflict significant harm on recipients of the document (after discussion with the patient) and finding a suitable ending for the document which is appropriate to the patients' overall message. Another session is arranged for the therapist to read the edited transcript to the participants, who are invited to make any editorial suggestions, including identifying errors of omission or commission. Once these 'generativity' documents are finalised they become the property of the patient, who can share it with anyone they choose, whenever they choose. We give them as many copies as they wish. At the start of the therapy, we ask patients who they intend to leave the 'generativity' document to, as this enables the therapist to guide the patient to cover the areas most relevant to the intended recipient(s). However, patients can change their mind about this at any time. They may decide not to give their 'generativity' document to anyone, or give it to other recipients. We do not exclude patients who do not wish to pass on their document. If they do not wish to bequeath it to anyone they can either destroy it or leave it with their other personal documents such as their will, diaries and important letters. The therapist discusses this with any patients who decide not to bequeath their document.

Since participants' conditions can fluctuate rapidly, the timing of the contacts can be relaxed and meetings rescheduled. If a participant's condition deteriorates, meetings are rescheduled up to three times before sensitively withdrawing them from the study. The therapist makes detailed notes of her experiences of giving each intervention and any deviations from the protocol. One in three therapy transcripts is randomly selected for review by the principal investigators. A quality assurance protocol has been developed to assess adherence to the Dignity Therapy protocol and deviations from the protocol will be reported as part of the feasibility study. This includes whether or not the therapist was respectful and asked the questions from the Dignity Therapy protocol appropriately, and whether or not the editing process was carried out in accordance to the protocol.

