**Figure 1 F1:**
[figure not shown]
**Recruitment and follow-up procedure**.

Before consent is taken from patients who have expressed an interest in taking part, the research assistant checks they have fully understood the patient information sheet before obtaining written consent from those who are willing to take part. As a final check patients are screened with the Blessed Orientation Memory Concentration Test [8] to assess cognitive functioning after the consent procedure. It has been suggested by [name] (personal communication) that Dignity Therapy is not suitable for patients with a score equal to or greater than 15. In such cases patients are excluded. This is done sensitively: the research assistant spends some time chatting with them about neutral topics. This approach has worked successfully in a previous study[9]. The proportion of patients excluded at this stage will be reported. Oncologists in the Trusts have been informed of the study and General Practitioners will be informed of their patients' involvement.

Following the consent procedure, participants are asked to complete the baseline measures. They are then randomized. Those in the intervention group are given the framework of therapy questions (Appendix 1) so that they have an opportunity to think about their answers before the therapy interview. The therapist arranges to conduct the dignity therapy interview as soon as possible after recruitment (usually within two to three days), in the location most suited to the patient and in the most private area available if they are in hospital. Since the condition of participants could fluctuate rapidly, the timing of the contacts are sometimes adjusted and meetings rescheduled. If a participant's condition deteriorates, meetings are rescheduled up to three times before sensitively excusing them from the study. This, and the feasibility of following up with people if they leave hospital, will also be reported and taken into account when developing the RCT. Participants in the control group are reminded that they will still have the opportunity to talk to the researcher about how they are feeling and about their views on taking part in the study.

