### Outcomes

Both quantitative and qualitative outcomes are assessed (Table 1). These are collected from patients by face-to-face interviews at two time-points: approximately one (T2) and four weeks (T 3) after the dignity document has been completed, and the equivalent in the control group. This longer-term follow-up has not been included in the previous evaluation of Dignity Therapy, or in the current trials being conducted by [name] and colleagues. However, we believe it is important to evaluate the longer-term impact of the intervention. The feasibility of doing this is explored as part of this feasibility study. Quantitative measures have been validated and are fairly quick and easy to use. Qualitative interview schedules have been developed for the study.

**Table 1 T1:** Measures for each time point

	**Patients**		**Family/friends**	
	Intervention	Control	Intervention	Control

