### Analyses

#### Quantitative data

In view of the relatively small sample size, analyses will be mainly descriptive, however, between and within participant comparisons of outcomes will be conducted and the appropriate effect size estimates reported. Either parametric or non-parametric tests will be used, depending on the distribution of the data. The intervention and control group will be compared on the main outcome (a sense of dignity) and secondary outcomes (distress, hopefulness, quality of life and palliative care outcomes). We will also compare Time 2 and Time 3 follow-up with baseline for both groups on these measures, using a paired test. The two groups will also be compared on demographic characteristics and baseline measures. We will also report recruitment rates and compare drop-out rates and missing data in the two groups.

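### Exhausted rescheduling takes a deteriorating patient out of the whole study, and intervention patients have two more meetings at which it can apply, so loss of T2 and T3 outcomes can differ by arm

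*Protocol article*

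**What the plan says.** The rule appears twice in the protocol article. The intervention: "meetings are rescheduled up to three times before sensitively withdrawing them from the study". Recruitment procedure (text after Figure 1): "meetings are rescheduled up to three times before sensitively excusing them from the study". In both places the trigger is a decline in the participant's condition, neither place restricts the rule to one arm, and the consequence is leaving the study. The reason given is clinical instability: "Since participants' conditions can fluctuate rapidly, the timing of the contacts can be relaxed and meetings rescheduled".

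The contacts to which it can apply are these:

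- Study design: "Consenting participants have been randomly allocated to one of these two groups after baseline (T1) measures have been collected". Baseline is therefore not a post-randomization meeting.
- Recruitment procedure, intervention arm only: "The therapist arranges to conduct the dignity therapy interview as soon as possible after recruitment".
- The intervention, intervention arm only: "Another session is arranged for the therapist to read the edited transcript to the participants".
- Outcomes, both arms: interviews "approximately one (T2) and four weeks (T 3) after the dignity document has been completed, and the equivalent in the control group".
- Control group: no fewer than three research-assistant interviews, a number that T1, T2 and T3 already account for.

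Under Quantitative data the plan is to "compare drop-out rates and missing data in the two groups". Under Participants, one stated aim is an effect-size estimate for a later trial.

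**The concern.** The rule does not separate stopping therapy from ending outcome collection. A patient too unwell to complete the therapy interview or the read-back after repeated attempts leaves before T2. A control with the same temporary decline has no meeting to miss at that time and can still provide T2. A rule with identical wording thus gives the two arms different exposure to removal, and the removal is related to health.

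The timing of follow-up adds to this. T2 and T3 are counted from completion of the document, so an intervention patient without one has no defined T2 or T3 date, and the article does not say that their outcomes are still sought.

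Three results are at stake: the between-group effect size meant for Phase III planning, the drop-out comparison (itself a feasibility result), and the acceptability views of patients who could not finish therapy.

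**Working it through.** The protocol gives no rescheduling, deterioration or drop-out rate, so there is no figure to reproduce. The meeting counts come from the text; the failure rate is an assumption.

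**Meetings after randomization, intervention vs control**

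- To T2: therapy interview, read-back and T2, against T2 alone: 3 vs 1.
- To T3: one more in each arm: 4 vs 2.

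**Model.** Let r be the assumed chance that any one attempt fails through deterioration, equal in both arms, and k the number of meetings. Removal needs four failures: the original appointment and three reschedulings. The text does not say whether the limit of three counts per meeting or over the whole study, so both are shown.

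- Per meeting: loss = 1 − (1 − r⁴)^k.
- Cumulative: loss = 1 − Σ(j = 0 to 3) C(j+k−1, j)(1−r)^k r^j, the chance of four failed attempts before k completed meetings.

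**Worked case, r = 0.4, to T3**

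- Per meeting: r⁴ = 0.0256. Intervention 1 − 0.9744⁴ = 9.9%; control 1 − 0.9744² = 5.1%.
- Cumulative: intervention 1 − 0.6⁴ × (1 + 1.6 + 1.6 + 1.28) = 1 − 0.1296 × 5.48 = 29.0%; control 1 − 0.6² × (1 + 0.8 + 0.48 + 0.256) = 1 − 0.36 × 2.536 = 8.7%.

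**Loss, intervention vs control**

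| r (assumed) | Per meeting, T2 | Per meeting, T3 | Cumulative, T2 | Cumulative, T3 |
|---|---|---|---|---|
| 0.2 | 0.5% vs 0.2% | 0.6% vs 0.3% | 1.7% vs 0.2% | 3.3% vs 0.7% |
| 0.3 | 2.4% vs 0.8% | 3.2% vs 1.6% | 7.0% vs 0.8% | 12.6% vs 3.1% |
| 0.4 | 7.5% vs 2.6% | 9.9% vs 5.1% | 17.9% vs 2.6% | 29.0% vs 8.7% |

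Forty patients in blocks of two give 20 per arm. At r = 0.4 the expected losses to T3 are 2.0 vs 1.0 patients (per meeting) or 5.8 vs 1.7 (cumulative). A two-sided 5% comparison of two proportions with 20 per arm would detect these differences with power of about 8% and 37%.

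**Selection, illustration only.** The model above treats attempts as independent, so it says nothing about who is lost. Suppose instead that each patient has a fixed frailty that raises r (mean r 0.33 or 0.45) and correlates 0.3 or 0.5 with the outcome, and that therapy has no effect. The patients remaining at T3 then differ between arms by 0.02 to 0.07 SD (per meeting) or 0.05 to 0.13 SD (cumulative), in the direction that favours therapy. Every input here is assumed.

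**The case against.** The strongest counter-argument is that lasting decline removes patients from both arms. Control T2 is set at an equivalent time, so a control who declines and does not recover would usually miss it too. Excess loss then comes mainly from patients who fail repeated attempts and later recover enough for an outcome interview. This stands: it limits the size and is a reason to state no single figure. It does not remove the unequal exposure, because patients whose condition fluctuates are the ones the protocol expects.

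A reader might put a flat 5% or 10% chance of removal on each meeting and obtain 14.3% vs 5% (1 − 0.95³ against 0.05) or 27.1% vs 10% (1 − 0.90³ against 0.10) at T2. The documents do not support these inputs. With a per-meeting limit they imply that about 47% (0.05^¼) or 56% (0.10^¼) of attempts fail. Independent removal at a constant rate also says nothing about selection on health.

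A reader might infer that any failure to complete therapy ends participation, or that the nominated relative leaves with the patient. Neither is in the text. The trigger is deterioration after rescheduling is exhausted, and bereavement interviews are planned with all nominated family and friends.

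It is also true that the protocol records uncompleted interventions with reasons, will report these withdrawals and take them into account for the later trial, and compares drop-out by arm. This is a small pilot with mainly descriptive analyses. Such reporting discloses the loss, but it neither recovers the outcomes nor separates the effect of the rule from that of the therapy.

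**Conclusion.** The point holds as a design weakness of moderate weight. As written, the rule ends study participation on health grounds, and the intervention arm meets it at two more post-randomization meetings. If the failure rate per attempt is the same in both arms and lies strictly between 0 and 1, intervention loss exceeds control loss under either way of counting the limit. The drop-out comparison therefore partly reflects the number of meetings.

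The size is not known. Over assumed failure rates of 20% to 40% it runs from negligible (under one patient of 20) to serious (about 6 vs 2 of 20), and how the limit is counted matters as much as the rate.

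A reader might go further and conclude that the PDI comparison is materially biased in favour of therapy. That is possible if the patients lost are also those with more dignity-related distress. The documents give neither that relation nor a rate of loss, so only a possible distortion can be claimed.

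**What to change.** Leave the rescheduling rule for therapy sessions as it is, and amend The intervention and Recruitment procedure to say that exhausting it ends those sessions only. Then:

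- Offer T2 and T3 to every randomized patient who is able and has not withdrawn consent, as a PDI-only or telephone contact where a full interview is not possible.
- For intervention patients without a completed document, time T2 and T3 on the same schedule as the control group.
- Report therapy non-completion, missed outcome visits, withdrawal of consent and death separately by arm.

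The cost is a change of wording, a few extra contacts with frail patients, whose burden has to be weighed, and some reduced-form outcome data.
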